# Rationale and design of the randomized, multicenter, open-label, controlled POLBOS 3 trial aimed to compare regular drug-eluting stents versus the dedicated coronary bifurcation sirolimus-eluting BiOSS LIM C stent

**DOI:** 10.1097/MD.0000000000015106

**Published:** 2019-04-05

**Keywords:** BiOSS LIM C, coronary bifurcations, non-LM, sirolimus-eluting stent

## Abstract

**Introduction::**

Coronary bifurcations are encountered in about 15% to 20% of percutaneous coronary interventions (PCIs). They are considered technically challenging and associated with worse clinical outcomes than nonbifurcation lesions. The BiOSS LIM C is a dedicated bifurcation balloon expandable stent made of cobalt-chromium alloy (strut thickness 70 μm) releasing sirolimus (1.4 μg/mm^2^) from the surface of a biodegradable coating comprised of a copolymer of lactic and glycolic acids.

**Conclusion::**

The aim of the randomized, multicenter, open-label, controlled POLBOS III trial is to compare BiOSS LIM C with limus second-generation drug-eluting stents (DES) in the treatment of non-left main stem coronary bifurcations (ClinicalTrials.gov NCT03548272).

## Introduction

1

The BiOSS (Bifurcation Optimization Stent System) Clinical Program has started in 2008. The first BiOSS stent was a bare metal one (stainless steel), but shortly after a paclitaxel-eluting version was introduced into the market—the BiOSS Expert stent (CE Mark 2010), and in 2012, sirolimus-eluting BiOSS LIM stent was developed. The obtained results both in registries and clinical randomized trials POLBOS I and POLBOS II^[1–6]^ as well as in everyday practice were satisfactory,^[7–9]^ but still a way for improvement has been looking for. Relatively large neointimal growth associated with thick struts (120 μm) was a reason to design a cobalt-chromium sirolimus-eluting version—BiOSS LIM C stent. BiOSS LIM C stent preclinical and preliminary clinical utility has been already confirmed.^[10,11]^

The aim of this trial (POLBOS 3) is to compare BiOSS LIM C with the limus second-generation drug-eluting stents (DES) in the treatment of nonleft main (non-LM) coronary bifurcations.

## Material and methods

2

### Device

2.1

The BiOSS LIM C is a dedicated bifurcation balloon expandable stent made of cobalt-chromium alloy (strut thickness 70 μm) releasing sirolimus (1.4 μg/mm^2^) from the surface of a biodegradable coating comprised of a copolymer of lactic and glycolic acids (PGLA). The degradation of the polymer lasts approximately 8 weeks. The BiOSS LIM C stent consists of 2 main separate parts with different diameters: wider proximally and distally smaller. The proximal part is always a shorter than the distal one (45% vs 55%, respectively). The ratio of the proximal part to the distal one varies between 1.15 and 1.3, ensuring physiological compatibility and optimal flow conditions. There is a 2.0 to 2.4 mm middle zone with 2 connecting struts after the BiOSS stent implantation. This zone ensures “self–positioning” of a stent after balloon deflation, as well as the opening to side branch. There are 3 lengths (16, 19, and 24 mm) of BiOSS stents available on the market. The nominal foreshortening of the stent is less than 0.5% and the stent strut/vessel area ratio varies between 15% and 18%.^[12]^

### Study population and study design

2.2

Five hundred eighteen patients with symptomatic stable coronary artery disease or NSTE-ACS qualified for PCI in non-LM coronary bifurcation will be screened, and enrolled if informed consent form is signed and all inclusion criteria and none exclusion criteria are met. Inclusion criteria and exclusion criteria are detailed in Table 1.

**Table 1 T1:**
[figure not shown]
Inclusion and exclusion criteria.

Subjects will be 1:1 randomized to a BiOSS LIM C stent versus DES group. The following DES will be allowed: Xience (Abbott Laboratories, Chicago, IL), Resolute Onyx (Medtronic, Dublin, Ireland), Orsiro (Biotronik, Berlin, Germany), and Synergy (Boston Scientific, Marlborough, MA). Patients will be followed, according to the protocol (ClinicalTrials.gov NCT03548272) (Fig. 1). Study protocol is compliant with SPIRIT guidelines.^[13]^ Independent Ethics Committee approved the study protocol (No. 14/2018).

**Figure 1 F1:**
[figure not shown]
POLBOS 3 flow chart.

### Study methodology

2.3

Single stent implantation in the main vessel-main branch across a side branch is the default strategy (provisional T-stenting, PTS) in all patients enrolled. Bifurcation lesions are assessed according to Medina classification using an index of 1 for stenosis greater than 50% and 0 for no stenosis (visual estimation).^[14]^ There is no restriction regarding lesion length in patient selection. If required, additional stent can be implanted (Alex Plus in the BiOSS Lim C Group).^[15]^ A stent in a side branch (Alex Plus in the BiOSS Lim C Group) should be implanted only if there is proximal residual stenosis greater than 70% after balloon dilatation and/or significant flow impairment after main vessel—main branch stenting and/or a flow-limiting dissection.

The implantation protocol for bifurcation is as follows:

(1)wiring of both branches;(2)main vessel predilatation according to the operator's decision (recommendation BA/MB ratio close to 1:1);(3)side branch predilatation according to operator's decision, however with small balloon;(4)stent implantation (inflation for at least 20 seconds);(5)proximal optimization technique (POT);(6)side branch postdilatation or side branch stent implantation if necessary (proximal residual stenosis greater than 70% after balloon dilatation and/or significant flow impairment after main vessel—main branch stenting and/or a flow-limiting dissection);(7)final kissing balloon inflation at operator's discretion (mandatory only if 2-stent technique applied);(8)Second POT (re-POT)(9)Additional dilatation of a distal part of a stent (distal optimization technique - DOT) with a NC balloon at operator's discretion.

In patients with ACS, loading dose of ticagrelor (180 mg) or clopidogrel (600 mg) will be given, and if needed also the loading dose of acetylsalicylic acid (ASA) was applied (300 mg). In planned procedures, 72 hours before PCI, each patient will receive ASA (75 mg/24 h) and clopidogrel (75 mg/24 h). All procedures will be performed in a standard way via radial or femoral access using 6 or 7 Fr guiding catheters. After insertion of the arterial sheath, each patient received unfractionated heparin (100 IU/kg). Additional bolus will be given to maintain an activated clotting time > 250 seconds. Dual antiplatelet therapy (ASA 75 mg q.d. quaque die (once a day) and clopidogrel 75 mg q.d. or ticagrelor 90 mg b.i.d. bis in die (twice a day)) will be prescribed for 12 months.

All patients will have TnI, CK, and CK-MB levels examined before the procedure, 6 and 24 hours after. Periprocedural myocardial infarction (type 4a) will be assessed according to the third universal definition (patients with NSTEMI were excluded from this assessment).^[16]^

Quantitative coronary angiography (QCA) analysis before and after the procedure will be performed with the use of the dedicated bifurcation QCA software (CAAS 11.0; Pie Medical Imaging, Maastricht, the Netherlands).

### Follow-up

2.4

Clinical visits will be performed at 30 days and 12 months, and telephone visit will be performed at 3 and 6 months. At the clinical follow-up visit, clinical status (Canadian Cardiovascular Society Classification), adverse events according to protocol, hospitalization, and medication intake will be evaluated.

### Endpoints

2.5

The primary endpoint is the rate of major cardiovascular events rate (cardiac death, myocardial infarction, target lesion revascularization) at 12 months. The secondary endpoints are as follows: all-cause death; cardiovascular death—all deaths considered cardiovascular death if not proved otherwise; myocardial infarction—more than 5 times upper limit normal (ULT) increase of troponin, CK-MB, total CK or MRI-detected new areas of late-gadolinium enhancement, associated with symptoms suggesting ischemia, and/or appearance of new-Q waves on surface ECG; target lesion revascularization—any reintervention in previously implanted stent and/or ± 5 mm proximal/distal from stent borers; stent thrombosis—according to Academic Research Consortium definition—definite, probable, possible; early—1 to 30 days after PCI, late—30 days—12 months after PCI, very late—after 12 months after initial PCI, stroke—defined as new persistent neurology deficit, and bleeding—defined according to TIMI group as major and minor.

An independent Clinical Event Committee is built by 3 cardiologists, who are otherwise not involved in the trial. Each clinical event will be adjudicated independently and blindly by 2 members of Committee. In case of disagreement, the third member will be involved and joint agreement should be reached.

### Statistics

2.6

The mean incidence of MACE rates with currently available stents at 1 year is 10% to 15%. Assuming noninferiority margin (delta) of 8%, a total sample size of 518 patients (with drop-out rate of 5%), 259 patients per group, will be necessary (type I error: 0.05, type II error: 0.2, statistical power 80%). During the analysis, continuous variables in the 2 groups will be compared by unpaired Student *t* test, Mann–Whitney test, or analysis of variance (ANOVA) test, as appropriate. Categorical variables in the 2 groups will be compared with Fisher exact or Chi-square tests, as appropriate. Difference in event-free survival between the 2 groups will be evaluated by applying the Kaplan–Meier curves. Results will be adjusted by Cox-regression multivariate analysis where needed, as appropriate. A probability value of *P* < .05 is considered as statistically significant.

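### The trial is sized for non-inferiority with an 8-point margin, but none of the stated analyses tests that margin and no success rule is given

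*Protocol article*

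**What the plan says.** All the relevant text is in the protocol article.

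- **Endpoint (2.5 Endpoints).** "The primary endpoint is the rate of major cardiovascular events rate", a composite of cardiac death, myocardial infarction and target lesion revascularization at 12 months. It is a binary outcome per patient.
- **Design (2.6 Statistics).** One-year MACE with current stents is put at 10% to 15%. The number of patients is then derived from the margin: "Assuming noninferiority margin (delta) of 8%, a total sample size of 518 patients", allowing 5% drop-out, with "type I error: 0.05, type II error: 0.2, statistical power 80"%. The sidedness of the type I error is not given.
- **Analysis (2.6 Statistics).** "Categorical variables in the 2 groups will be compared with Fisher exact or Chi-square tests, as appropriate". Continuous variables get t, Mann-Whitney or ANOVA tests. Kaplan-Meier curves serve to look for a difference in event-free survival, with Cox adjustment where needed. A P value under .05 "is considered as statistically significant".

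The margin appears only in the sample-size sentence. The stated aim, in the Abstract, the Introduction and the Discussion, is simply to compare the stents.

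**The concern.** A Fisher or chi-square test takes no difference as its null hypothesis. Rejecting that null says the arms differ; failing to reject it says only that a difference was not detected. Neither result shows that BiOSS LIM C is less than 8 points worse than DES, which is the question that fixed the sample size. Kaplan-Meier curves and a Cox model do not address the margin either, unless an interval from them is set against it.

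The article therefore names its tests and its significance criterion, and they do not fit the design it states in the same paragraph. The trial's main conclusion is at stake. Without a stated rule, the reader of a P value at or above .05 has nothing in the article that separates non-inferiority shown from non-inferiority not shown. In an open-label trial that rule should be on record before results are known.

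**Working it through.** **Inputs.** From 2.6 Statistics: margin 8% (read as percentage points; the scale is not stated), control rate 10% to 15%, type I error 0.05, power 80%, drop-out 5%, 259 per group. From 2.2: allocation 1:1. Assumed, because not stated: equal true rates in the two arms for the sample size. Sidedness is tried both ways.

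**1. The stated sample size.** For equal rates p and margin d, n per arm = (z_alpha + z_beta)² × 2p(1 − p) / d².

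- p = 0.15, d = 0.08, one-sided 0.05: (1.645 + 0.842)² × 2 × 0.15 × 0.85 / 0.0064 = 246.3. Dividing by 0.95 gives 259.3, so 259 per group and 518 in total, as stated.
- One-sided 0.025 gives totals of 466 at 10%, 568 at 12.5% and 660 at 15%. It reaches 246 per arm only at a rate of about 11.3%.

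The figure of 518 is therefore coherent as a non-inferiority sample size.

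**2. Evaluable patients.** 259 × 0.95 = 246 per arm.

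**3. A stent worse by exactly the margin.** The table sums exact binomial probabilities over all outcomes with 246 per arm. The margin test is passed when the difference plus z times its unpooled standard error is below 0.08.

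| True rates, DES vs BiOSS | Chi-square P ≥ .05 | Fisher P ≥ .05 | Margin test passed, one-sided 0.05 | Margin test passed, one-sided 0.025 |
|---|---|---|---|---|
| 10% vs 18% | 26.9% | 31.1% | 5.2% | 2.6% |
| 12.5% vs 20.5% | 33.0% | 37.2% | 5.2% | 2.6% |
| 15% vs 23% | 37.9% | 42.2% | 5.1% | 2.6% |

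Hand check of the last row by normal approximation: chi-square is non-significant, to a close approximation, when the observed difference is below 1.96 × √(2 × 0.19 × 0.81 / 246) = 0.0693. The standard error under the true rates is √((0.15 × 0.85 + 0.23 × 0.77) / 246) = 0.0352. The probability is Φ((0.0693 − 0.08) / 0.0352) ≈ 0.38.

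**4. One possible result.** Take 46/246 on BiOSS (18.7%) and 31/246 on DES (12.6%). Chi-square P = 0.063 and Fisher P = 0.082, so neither is significant. The difference is 15/246 = 6.1 points with standard error 3.26 points. The upper limit is 6.1 + 1.645 × 3.26 = 11.5 points (two-sided 90% interval) or 6.1 + 1.96 × 3.26 = 12.5 points (two-sided 95% interval). Both exceed 8, so non-inferiority is not shown on either reading.

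**5. Power of a margin test with 246 per arm and equal true rates.**

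| True rate in both arms | One-sided 0.05 | One-sided 0.025 |
|---|---|---|
| 10% | 90% | 84% |
| 12.5% | 85% | 76% |
| 15% | 80% | 70% |

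**The case against.** The strongest reply is that this is an omission in a condensed article. A fuller protocol exists and an SAP may; the primary estimator and the interval rule are the sort of detail they carry. The sentence on categorical variables is generic and is not tied to the primary endpoint, so it could be meant for baseline and secondary variables. A P < .05 criterion could also apply to a non-inferiority P value.

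Much of this stands. Two stronger readings that a reader might draw are not supported:

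- **That the margin will never be tested.** This holds only for the analysis the article states. Documents not shown may contain the test.
- **That the plan counts a non-significant P as success.** No passage says so. The 27% to 38% (31% to 42% by Fisher) are error rates of a possible misreading, not of a documented decision rule.

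Nor can 5% be called the error rate of a margin test without qualification, because the sidedness is unstated; at one-sided 0.025 it is 2.6%.

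What does not stand is that nothing needs correcting. The article goes beyond silence: it lists its tests and its criterion, gives no other test for a binary rate, and does not exempt the primary endpoint.

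**Conclusion.** The point holds in limited form. The design is non-inferiority and its sample size is consistent, but the stated analysis cannot by itself support a non-inferiority conclusion, and the article gives no rule for one.

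If a non-significant chi-square were taken as success, a stent worse by the whole margin would pass about five to seven times as often as under a one-sided 0.05 margin test (26.9/5.2 = 5.1; 37.9/5.1 = 7.5), and roughly ten to fifteen times as often as under one-sided 0.025.

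These figures assume 246 evaluable patients per arm, a margin in percentage points, and control rates within the article's 10% to 15%. The mismatch between design and stated tests depends on none of them. If the full protocol or SAP already contains the margin test, what remains is to bring the article's wording into line with it.

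**What to change.** Add one paragraph to the protocol or SAP, or confirm that it is already there:

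- **Primary analysis.** The BiOSS-minus-DES difference in 12-month MACE with a confidence interval, for example Farrington-Manning, or Kaplan-Meier estimates with Greenwood standard errors.
- **Success rule.** Claim non-inferiority only if the upper limit is below 8 percentage points.
- **Sidedness.** State it. A one-sided 95% limit (the upper end of the two-sided 90% interval) is the reading that reproduces 259 per group at a 15% rate with 80% power. A one-sided 97.5% limit is the stricter choice; with the same patients its power is about 84% at 10% and 70% at 15%, so holding 80% power at 15% would take 660 patients.
- **Other P values.** Limit Fisher, chi-square and Cox P values to baseline, secondary and supportive comparisons, and say that they do not support a non-inferiority claim.

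The cost is wording only. No extra patients or data are needed, unless the sponsor chooses the stricter limit and wants to keep 80% power at the higher event rates.

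### The Cox adjustment is conditional, and the article does not say which result decides non-inferiority; a hazard ratio also cannot be read against the 8-point margin

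*Protocol article*

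**What the plan says.** The Endpoints section defines the outcome as a proportion at a fixed time: "The primary endpoint is the rate of major cardiovascular events rate (cardiac death, myocardial infarction, target lesion revascularization) at 12 months". The Statistics section sizes the trial on that scale. It gives the expected rate ("The mean incidence of MACE rates with currently available stents at 1 year is 10% to 15" per cent), the margin ("Assuming noninferiority margin (delta) of 8" per cent) and the number of patients ("a total sample size of 518 patients (with drop-out rate of 5%), 259 patients per group, will be necessary").

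The same section then lists Fisher or chi-square tests for categorical variables and Kaplan-Meier curves for event-free survival, followed by the sentence at issue: "Results will be adjusted by Cox-regression multivariate analysis where needed, as appropriate". None of these is named as the analysis that decides the primary comparison. Type I error is 0.05, with no statement of one- or two-sided.

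Three kinds of baseline information are visible elsewhere. The trial enrols "patients with symptomatic stable coronary artery disease or NSTE-ACS qualified for PCI in non-LM coronary bifurcation". In Study methodology, "Bifurcation lesions are assessed according to Medina classification" and "Quantitative coronary angiography (QCA) analysis before and after the procedure will be performed".

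**The concern.** There are two linked problems.

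- **The condition.** In a randomised comparison any baseline imbalance is due to chance. The reason to adjust is that a variable predicts the outcome, and this can be settled beforehand. A rule that adjusts only if needed, without saying which result counts, allows two answers to one question. If either may support the claim, the false non-inferiority rate exceeds its nominal level.
- **The scale.** The margin is a difference in 12-month rates. The only adjusted method named gives a hazard ratio. If that were the result relied on, the article would supply no criterion for judging it.

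At stake is whether the single primary claim rests on one analysis on the scale for which the trial was sized.

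**Working it through.** **Inputs.** From the Statistics section: control rate 10% to 15%, margin 8%, type I error 0.05, power 80%, 259 per group, drop-out 5%. Evaluable patients per arm: 259 × 0.95 = 246. Covariate strengths are assumed, because the article gives none.

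**1. The plan's own figure.** With equal true rates p and absolute margin d:

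n per arm = (z for alpha + z for power)² × 2p(1−p) / d²

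With p = 0.15, d = 0.08 and one-sided 0.05: (1.645 + 0.842)² × 0.255 / 0.0064 = 246.3. Then 246.3 / 0.95 = 259.3 per arm, which matches 259; rounding up at each step gives 260 per arm, 520 in total. One-sided 0.025 with a rate of 11.3% also gives 518. The article does not say which pair was used. Either way, 518 comes from an unadjusted calculation on an absolute 8-point difference.

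**2. The scale.** Under proportional hazards, the hazard ratio equivalent to the margin is HR = ln(1−p−0.08) / ln(1−p).

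- p = 0.15: ln 0.77 / ln 0.85 = 1.61
- p = 0.10: ln 0.82 / ln 0.90 = 1.88

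Conversely, a hazard ratio of 1.61 at a 10% control rate gives 1 − 0.90^1.61 = 15.6%, a difference of 5.6 points. A hazard ratio of 1.88 at 15% gives 1 − 0.85^1.88 = 26.3%, a difference of 11.3 points. Within the article's own range of rates, no single hazard ratio stands for 8 points.

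**3. Free choice between two results.** Trials were simulated at the margin (15% v 23%, 246 per arm, 6,000 runs, two or four standard-normal covariates with coefficients 0.3 to 0.5 per SD). Both analyses estimate a risk difference.

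| Covariates | Unadjusted | Adjusted | Either passes |
|---|---|---|---|
| 2, coefficient 0.3 | 4.8% | 4.6% | 5.3% |
| 2, coefficient 0.5 | 5.1% | 5.1% | 6.3% |
| 4, coefficient 0.4 | 5.1% | 5.1% | 6.4% |

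Simulation error is about 0.3 points (√(0.05 × 0.95 / 6000) = 0.0028). A second simulation (three or five covariates, odds ratio 1.25-1.4 per SD, 3,000 runs) gave 5.6% to 6.1% for the better of the two. At nominal 2.5% the first set-up gave 3.0% to 3.4%.

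**4. Power from always adjusting on the risk-difference scale.** Power = Φ(0.08 / √(2p(1−p)(1−R²)/246) − z for alpha), where R² is the share of outcome variance explained (assumed). At p = 0.15:

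| R² | One-sided 0.05 | One-sided 0.025 |
|---|---|---|
| 0 (unadjusted) | 80.0% | 70.0% |
| 0.02 | 80.7% | 70.9% |
| 0.05 | 81.7% | 72.2% |
| 0.10 | 83.5% | 74.5% |

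Simulated power at one-sided 0.05 rose from 79.1% to 80.2%, from 79.7% to 81.8% and from 79.8% to 82.3% in the three covariate settings.

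**5. Cox adjustment.** With a true hazard ratio of 1 and 15% events, the mean standard error of the log hazard ratio was 0.236 unadjusted and 0.237 adjusted (0.235 v 0.236 and 0.235 v 0.237 in the other two settings). No gain in precision was detectable.

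**The case against.** The strongest reply is that this is a condensed article and the analysis plan is not shown. Covariate lists and model details are commonly left there, and their absence is not the point here. The Cox sentence directly follows the one on Kaplan-Meier curves and speaks of results in general, so it can fairly be read as supporting the survival analysis, with the primary rate compared unadjusted. That reading is open. However, the article does not state it, and the sentence it does print makes adjustment conditional for results without exception.

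Other parts of the reply stand and limit the point:

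- A reader might infer that adjustment will be chosen after the data are seen, or triggered by baseline significance tests. The article gives no timing and no trigger, and a plan not shown may fix both.
- A reader might infer that the trial loses planned power. It does not, because 518 is reproduced without any adjustment.
- The false-claim rates describe a choice between risk-difference analyses, not the Cox model that the article names. A search over many covariate subsets would inflate them further, but nothing in the article suggests such a search.
- An unadjusted primary risk difference, with Cox labelled supportive, would remove the ambiguity equally well. Fixed adjustment is an improvement and is not required for validity.
- QCA lesion length is not named as a recorded variable, and true bifurcation is not defined in the text shown.

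**Conclusion.** The point holds in limited form. The article states a conditional Cox adjustment, does not say which result decides non-inferiority, and names an adjusted method whose output cannot be compared with the stated margin. The scale mismatch follows from the article's own rates, with proportional hazards assumed for the conversion.

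The numerical consequences are modest and rest on assumed covariate strengths. The false non-inferiority rate is about 5.5-6.5% in place of 5% if either of two analyses may carry the claim. About 1-3 points of power are available from fixed risk-difference adjustment at a 15% event rate and one-sided 0.05. The design and sample size are not undermined. The sentence should be replaced because a better one costs little and removes the ambiguity entirely.

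**What to change.** Replace the sentence so that it states the following:

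- The primary 12-month MACE comparison is one covariate-standardised risk difference. A logistic model predicts each patient's risk under both stents, the predictions are averaged over all patients, and the two averages are subtracted. A robust or delta-method confidence interval is compared with the 8-point margin. State its confidence level, which also settles the sidedness of the 0.05.
- The model always includes, whatever the observed imbalance, clinical presentation (stable disease v NSTE-ACS) and Medina class, grouped in a way fixed in advance. A pre-procedure QCA measure is added only if it is recorded in all patients. The list should stay short: 492 evaluable patients (2 × 246) give about 49 events at 10% (0.10 × 492) and about 74 at 15% (0.15 × 492).
- The unadjusted risk difference is a sensitivity analysis.
- Cox models are supportive and do not decide the claim.

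The cost is slightly more programming and a rule for missing covariate values. No additional patients or visits are needed.
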